### Follow-up

Patients will be followed up by reviewing clinical records relating to their inpatient course, including data from serial troponin testing; other laboratory analyses; length of stay; all imaging investigations and procedures and details of any haemorrhagic complications. We will also contact the participant’s primary care practitioner after 60 days to obtain information about any additional relevant events occurring within 30 days of the initial ambulance call. In the small percentage of cases where participants do not have a primary care practitioner, we will contact participants directly after 30 days. If this is not possible and the participant is lost to follow up, then this will be recorded on the electronic case report form.

### Resource use

We will collect comprehensive data about secondary healthcare resource use at baseline and 30 days, which may be used to subsequently develop a cost-effectiveness model. Total direct healthcare costs will be identified and quantified according to the UK NHS perspective relevant to decision-makers within the NHS.^8^ At baseline, data will be collected with regards to the initial ambulance call, such as the date and time of the call, the time of ambulance dispatch to the patient, the time of arrival to the patient and whether a rapid response unit was dispatched. Resource-use data collected at 30 days will include: time (hours) and length (days) of hospital stay (total; on coronary care, high dependence and intensive care units); laboratory, radiological and cardiological investigations during the initial hospital stay; nature and duration of any procedures or cardiac surgery; management of haemorrhagic complications; details of admissions and further ED attendances. Data on resource use will be collected using structured data collection forms from patient medical records and supplemented by information obtained from the patient’s primary care practitioner at follow-up.

### Sample processing

On arrival at the destination hospital, the labelled whole blood sample that was drawn in the prehospital environment for research will either be sent to the hospital laboratory for processing and storage along with study-specific instructions, or this will be carried out by members of the local research team. The local laboratory personnel/research team members will test the whole blood for POC troponin using the Roche cobas h 232 TnT and the leftover will be centrifuged to separate out the plasma. The plasma will then be stored in separate aliquots and transferred to the freezer within 8 hours of collection, pending subsequent analysis in batches. The relevant manufacturers of commercially available assays have verified sample stability under these conditions.

The laboratory/research team will process a second lithium heparin sample, drawn by the research nurse, 1 hour (±30 min) after the initial prehospital blood draw. For this sample, the local laboratory personnel/research team will centrifuge the blood sample and the plasma will then be divided into separate aliquots. This will then be stored in the freezer within 8 hours of collection. As above, samples will be stored pending subsequent analysis in batches.

Plasma will later be analysed for POC troponin assays, as follows: Abbott i-Stat troponin I and LumiraDx troponin I by the central study team. Leftover plasma will continue to be stored at the central study site to permit evaluation of additional, new POC troponin assays when developed.

### Participant selection

We will prospectively approach patients who have called for an emergency (999) ambulance with symptoms that the attending paramedic suspects may have been caused by an ACS.

#### Inclusion criteria

Adult patients (>18 years).Called 999 for an emergency ambulance because they have experienced pain, discomfort or pressure in the:Chest.Epigastrium.Neck.Jaw.Upper limb without an apparent non-cardiac source (compatible with the American Heart Association case definitions).^9^
Attending paramedic suspects these symptoms may be caused by ACS.

#### Exclusion criteria

Patients with unequivocal evidence of ST-elevation myocardial infarction who are being immediately transferred for primary percutaneous coronary intervention.Patients in whom an alternative diagnosis (other than ACS) is suspected, which would necessitate transfer to hospital.Patients who have not experienced symptoms in the previous 24 hours.

Patients who are unable to provide written informed consent, either because they lack the mental capacity to provide written informed consent or because effective communication is not possible (eg, non-English speakers in the absence of adequate translation services).

### Sample size

The specificity of T-MACS is approximately 45%^10^ and the prevalence of the primary outcome in this cohort will be approximately 10%. Assuming that we identify an algorithm with 100% sensitivity and negative predictive value, the lower bound of the 95% CI would be>90% for sensitivity and>99% for negative predictive value with a sample size of 605 participants. Accounting for potential loss to follow-up and missing data (~5%–10% based on experience in previous similar studies), we plan to include a total of 700 participants.

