## Introduction

Chest pain is one of the most common reason for emergency hospital admission. Clinicians will suspect a diagnosis of acute coronary syndromes (ACS) in approximately half of the patients presenting to emergency departments (EDs) with chest pain, accounting for the majority of these admissions. However, less than 20% of those admitted to hospital on the suspicion of ACS actually have that diagnosis. Most of these admissions could be avoided with improved diagnostic technology.^1–3^

In recent years, there has been much work performed in the ED setting with the aim of rapidly risk-stratifying patients with cardiac chest pain with a view to early discharge of those who are at low risk. The Troponin-only Manchester Acute Coronary Syndromes (T-MACS) is a scientifically derived mathematical model that combines clinical and historical features with ECG and cardiac biomarker results to determine the probability of ACS and assign patients to one of four risk groups: very low risk (<2% probability), low risk (2%–5% probability), moderate risk (5%–95% probability) and high risk (probability ≥95%).

T-MACS has been shown to effectively reduce unnecessary hospital admissions when used in the ED.^4^ It identifies 45% of patients as eligible for safe, immediate discharge following a single blood test.^4 5^ This is demonstrably superior to other early rule-out strategies, including that recommended by National Institute for Health and Care Excellence (NICE) prior to publication of our findings. In addition to ‘ruling out’ a diagnosis of ACS and reducing the need for unnecessary investigations and hospital admission, T-MACS can also ‘rule in’ the diagnosis in approximately 5% of patients with 95% positive predictive value, facilitating early specialist treatment.^4–7^

The original T-MACS model relies on laboratory-based troponin testing. In the multicentre Bedside Evaluation of Sensitive Troponin (BEST) study, we have evaluated the accuracy of T-MACS with point-of-care (POC) troponin assays that use portable/handheld analysers, which could be used in ambulances. Results from the BEST study demonstrate that, with a contemporary POC test, T-MACS ‘ruled out’ ACS in 42.7% of patients with 95.5% sensitivity and 98.7% negative predictive value.^5^

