Using portable POC tests, T-MACS could remove the requirement for many patients with suspected ACS to be assessed in the hospital, enabling even earlier reassurance for patients and cost savings for the National Health Service (NHS). Given the high prevalence of chest pain, avoiding ED attendances will reduce crowding, which leads to more patient safety incidents and higher mortality. Similarly, avoiding unnecessary transfer to hospital will free up ambulances to answer other emergency calls. However, as blood tests will be taken sooner after symptom onset, it is not safe to assume that T-MACS will be accurate in the prehospital environment. We must formally evaluate its accuracy in that setting.

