## Discussion

Based on our experience with previous studies, if our findings are positive we will aim to achieve clinical implementation within 2 years. Clearly, this will involve additional work to demonstrate the feasibility and acceptability of ‘live application’ of T-MACS in the ambulance; to develop new clinical guidelines and training regimes and to robustly communicate the clinical and cost effectiveness of the strategy.

The recent update to NICE Guideline CG95 incorporated a novel diagnostic strategy (originally developed by our group) for in-hospital use based on data from observational studies with a similar design. Given that precedent, we anticipate that our findings will generate the evidence required by NICE to issue a recommendation for the clinical use of T-MACS with a POC troponin assay in the prehospital environment.

We also implemented T-MACS in the hospital environment primarily based on observational data. The algorithm has been applied in 8000 patients and has led to 2/3 patients being safely treated in an ambulatory care environment without requiring hospital admission. Health Innovation Manchester, with access to a Joint Commissioning Board, has adopted T-MACS as an exemplar project for rapid implementation across Greater Manchester. We will conduct a ‘phase 4 evaluation’ of that regional implementation, aiming to achieve more widespread clinical implementation within 24 months of completion. If the findings of the proposed study are positive, we will use a similar methodology to achieve rapid implementation in the prehospital environment.

If successfully implemented in practice, we anticipate that our findings will avoid the need for unnecessary ambulance transfers and hospital admission in approximately 40% of patients. As chest pain is the second most common reason for emergency ambulance calls and most common reason for emergency hospital admission, this is likely to have a substantial economic impact while reducing hospital overcrowding and its associated complications.

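### The sample size is justified only for a zero-miss result; the >99% NPV bound fails even there, and neither bound is likely at the 95.5% sensitivity the article cites

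*Protocol article*

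**What the plan says.** The Sample size section of the protocol article takes specificity as about 45% and AMI prevalence as about 10%. It then gives one precision scenario: "Assuming that we identify an algorithm with 100% sensitivity and negative predictive value", in which case "the lower bound of the 95% CI would be>90% for sensitivity and>99% for negative predictive value", "with a sample size of 605 participants". The recruitment target of 700 allows for 5 to 10% loss and missing data. The interval method is not named, and no scenario with a missed case is shown.

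The Introduction reports that, in the same group's earlier study, T-MACS with a contemporary point-of-care assay ruled out ACS in 42.7% of patients, "with 95.5% sensitivity and 98.7% negative predictive value". It adds that blood is drawn sooner after onset before hospital, so "it is not safe to assume that T-MACS will be accurate in the prehospital environment". The Primary analysis section applies the existing T-MACS algorithm, fixed in advance, at the 2% threshold. The Discussion says that "if our findings are positive we will aim to achieve clinical implementation within 2 years".

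**The concern.** There are two problems in one sentence.

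First, the NPV bound looks too high for the number of patients likely to be ruled out, even if no AMI is missed.

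Second, the zero-miss case is the only one shown. The article's own figure for this rule with a point-of-care assay is below 100% on both measures. The primary analysis tests a fixed rule, so no perfect rule will be selected from the data. A reader who wants to know how precise the study will be has figures only for the best possible outcome.

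The study is meant to inform whether some patients could avoid transport to hospital. The lower limits for sensitivity and NPV are the figures that bear most directly on that question.

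**Working it through.** **Inputs.** From Sample size: N = 605 (target 700), prevalence 10%, specificity 45%. From the Introduction: sensitivity 95.5%, NPV 98.7%. Assumption, because no method is named: two-sided 95% Clopper-Pearson (exact) limits. With no misses in n, the lower limit is 0.025^(1/n).

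**Expected counts at N = 605.**
- AMIs: 0.10 × 605 = 60.5, taken as 60.
- True negatives: 0.90 × 0.45 × 605 = 245.

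**Step 1. Reproduce the stated zero-miss bounds.**
- Sensitivity, 60/60: 0.025^(1/60) = 94.0%. The >90% statement holds.
- NPV, 245/245: 0.025^(1/245) = 98.5%. The >99% statement does not hold.
- Other intervals for 245/245: Wilson 98.5%, one-sided 95% exact 98.8%, Jeffreys 98.98%. All are below 99%.
- All 700 evaluable: 0.90 × 0.45 × 700 = 283.5 negatives; exact 98.7%, one-sided 98.95%. Only Jeffreys passes 99% here (99.1%), and only with no losses.
- Negatives needed for an exact two-sided limit above 99% with no misses: ln(0.025)/ln(0.99), rounded up, = 368. That implies N = 368/(0.90 × 0.45) ≈ 909.

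One possible origin of 605 is 299/(0.90 × 0.55) = 604.04, rounded up. This is a one-sided 95% requirement (299 negatives) with 55% in place of 45%. It is inference only; the article does not show the calculation.

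**Step 2. Precision at 95.5% sensitivity, about 60 AMIs.** Expected misses: 60 × 0.045 = 2.7. Under Binomial(60, 0.045) the most likely count is 2 (24.8%), followed by 3 (22.6%).

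| Missed AMIs | Sensitivity, exact lower limit | NPV, exact lower limit |
|---|---|---|
| 0 | 60/60: 94.0% | 245/245: 98.5% |
| 1 | 59/60: 91.1% | 245/246: 97.8% |
| 2 | 58/60: 88.5% | 245/247: 97.1% |
| 3 | 57/60: 86.1% | 245/248: 96.5% |

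**Step 3. Chance of a sensitivity limit above 90%.**
- With 60 AMIs, at most 1 miss is allowed. P(0) = 0.955^60 = 6.3%. P(1) = 60 × 0.045 × 0.955^59 = 17.8%. Unrounded, the sum is 24.2%.
- With 70 AMIs (all 700 evaluable), at most 2 misses are allowed (68/70 gives 90.06%). P(≤2) under Binomial(70, 0.045) = 38.5%.

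**Step 4. NPV above 99%.** The cited 98.7% is already below 99%. At 10% prevalence, 45% specificity and 95.5% sensitivity, the expected NPV is 245.0/(245.0 + 2.7) = 98.9%, also below 99%. With about 245 true negatives, no row of the table reaches an exact lower limit of 99%.

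**Step 5. Sensitivity to the interval method.** At an observed 95.5% and N = 605, the lower limit for sensitivity is 86.8% exact, 87.0% Wilson, 86.5% Agresti-Coull and 88.0% Jeffreys. Wald gives 90.3%. Wald has zero width at 100%, so it cannot be the source of the stated bounds.

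**Step 6. Attrition.** 605/0.95 = 637 and 605/0.90 = 673 (both rounded up), each below 700. The allowance for loss is adequate and is not part of this point.

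**The case against.** The strongest reply is that the sentence is openly conditional. It says what the limits would be if no case were missed, and does not promise that result. That stands. A reader might infer that the assumption contradicts the Introduction, but it does not. The Introduction gives a past estimate and says accuracy before hospital cannot be taken for granted, which is the reason for the study. It does not forecast worse accuracy.

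The benchmark is also imperfect. The 95.5% and 98.7% come from one contemporary assay and are stated for ruling out ACS, whereas the primary outcome here is AMI. Three assays and several decision aids will be examined. This also stands, so the 95.5% results illustrate rather than predict. It is still the only point-of-care performance figure for T-MACS that the article offers, and the primary analysis does use the fixed T-MACS algorithm.

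A reader might further treat 90% as the bar for the positive findings mentioned in the Discussion. The documents do not support that. In Sample size, 90% describes precision, and a success criterion may well sit in the full protocol or analysis plan, neither of which is shown. Nor would a result lead directly to patients being left at home: paramedics do not see the T-MACS output, all participants are transferred, and the article refers to a definitive randomised trial and to further work before use.

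None of this touches the NPV bound, which fails under the article's own zero-miss condition.

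**Conclusion.** The point holds in two parts.

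1. **An error in a stated figure.** With the article's own inputs, the zero-miss lower limit for NPV at N = 605 is about 98.5%, not above 99%. At 605 it stays below 99% under the exact, Wilson, Jeffreys and one-sided exact calculations. The sensitivity bound is correct.
2. **An incomplete justification.** At the cited 95.5% sensitivity, with about 60 AMIs, lower limits of about 86 to 88% for sensitivity and 96.5 to 97% for NPV are to be expected. The sensitivity limit exceeds 90% with a chance of about 24%, or about 38% if all 700 are evaluable. An NPV limit above 99% is not to be expected.

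These figures rest on 10% prevalence, 45% specificity, exact two-sided intervals, and a sensitivity for ACS carried over to AMI. The first part is certain given the inputs. The second is an illustration at the article's own benchmark. It makes the planning scenario optimistic, not self-contradictory, and it sets no threshold for success.

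**What to change.** In Sample size, keep N = 605 and the target of 700, and make three changes.

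- Correct the zero-miss NPV bound to about 98.5% (about 98.7% if all 700 are evaluable). If another method or other inputs were used, state them so that the figure can be reproduced.
- Name the interval method and say whether it is one-sided or two-sided.
- Add a scenario at the cited performance. For example: if true sensitivity is 95.5%, 2 to 3 of about 60 AMIs would be missed, with lower 95% limits of about 86 to 88% for sensitivity and 96.5 to 97% for NPV; the chance of a sensitivity limit above 90% is about 24% (38% with 70 AMIs). Note that 95.5% was reported for ACS.

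The cost is two or three sentences. No enrolment, procedure or analysis changes. The only downside is that the stated precision becomes less favourable.

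### The sample-size section claims an NPV lower limit above 99% with 605 participants; its own inputs give about 98.5%

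*Protocol article*

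**What the plan says.** The Sample size section of the protocol article gives all the inputs to its calculation. On specificity: "The specificity of T-MACS is approximately 45"%. On prevalence: "the prevalence of the primary outcome in this cohort will be approximately 10"%. On the result to be observed: "Assuming that we identify an algorithm with 100% sensitivity and negative predictive value". From these it concludes that "the lower bound of the 95% CI would be>90% for sensitivity and>99% for negative predictive value with a sample size of 605 participants". It then allows for roughly 5%–10% loss and missing data and arrives at 700 to be enrolled. The interval method is not named.

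The Introduction uses the same 45% for a different quantity, the share of all patients who can be discharged: "It identifies 45% of patients as eligible for safe, immediate discharge following a single blood test".

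Under Statistical analysis, the primary analysis is rule-out accuracy at the 2% probability threshold, with NPV among the measures to be reported with 95% confidence intervals.

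**The concern.** When no false negatives occur, the lower limit for NPV depends only on the number of patients ruled out. At 45% specificity fewer than half of the non-infarct patients are ruled out, so the NPV denominator is far smaller than 605. It looked too small to support a lower limit above 99%.

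NPV is the safety figure for the intended use, which is to leave very-low-risk patients at home. The article also plans to move towards implementation if the findings are positive. A reader of the Sample size section would believe that a perfect result excludes a missed-infarction rate of 1% or more among ruled-out patients. If the limit is really about 98.5%, it does not. The Introduction reports an NPV of 98.7% for T-MACS with a point-of-care assay in the emergency department. A lower limit of 98.5% would not exclude even that value, whereas a limit above 99% would.

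**Working it through.** **Inputs** (all from the Sample size section): N = 605; prevalence 10%; specificity 45%; no false negatives; 95% confidence interval, taken as two-sided.

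**Counts**
- Infarctions: 605 × 0.10 = 60.5, taken as 60.
- True negatives: 605 × 0.90 × 0.45 = 245. With no false negatives this is the whole NPV denominator.

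**Formula.** For n successes out of n, the exact (Clopper-Pearson) two-sided 95% lower limit is 0.025^(1/n). The Wilson limit is n/(n + 1.96²) = n/(n + 3.84).

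**Sensitivity claim (above 90%).** 0.025^(1/60) = 94.0%. It holds.

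**NPV claim (above 99%) at 605**

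| Interval, n = 245 | Lower limit |
|---|---|
| Exact: 0.025^(1/245) | 98.51% |
| Wilson: 245/248.84 | 98.46% |
| Agresti-Coull | 98.14% |
| One-sided 95% exact, or mid-P: 0.05^(1/245) | 98.78% |
| Jeffreys, equal-tailed | 98.98% |
| Likelihood ratio: exp(−3.84/(2 × 245)) | 99.22% |
| Jeffreys, one-sided or highest-density | 99.22% |

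Only the last two exceed 99%. The likelihood-ratio interval would need just 192 true negatives, or 192/(0.90 × 0.45) = 475 participants, so it does not explain a choice of 605.

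**Larger N, exact method**
- 630 evaluable (700 less 10%): 255 true negatives, 98.56%.
- 665 evaluable (700 less 5%): 269 true negatives, 98.64%.
- 700 evaluable: 283.5, taken as 284, true negatives, 98.71% (Wilson 98.67%).

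**The other reading of 45%.** If it is the share of all patients ruled out, there are 0.45 × 605 = 272 true negatives. The lower limit is 98.65% exact, 98.61% Wilson and 98.91% (rounded from 98.905%) one-sided or mid-P. Equal-tailed Jeffreys gives 99.08% on this reading.

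**What a limit above 99% would take**
- Exact: ln(0.025)/ln(0.99) = 367.04, so 368 true negatives; 368/(0.90 × 0.45) = 909 evaluable. At 5%–10% loss, 909/0.95 = 957 to 909/0.90 = 1,010 enrolled.
- Wilson: 381 true negatives, 941 evaluable.
- Holding N at 605, the exact method would need a specificity of 368/544.5 = 68%.

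**Can 605 be reproduced?** Not from the stated inputs with any method in the table. One route does give it: 0.05^(1/n) exceeds 99% from n = 299, and 299/(0.90 × 0.55) = 604.04, which rounds up to 605. That would mean a one-sided (or mid-P) limit with 55%, the complement of the stated specificity, used as the ruled-out share. With the stated 45% the same formula gives 299/(0.90 × 0.45) = 739. This is inference; nothing in the article confirms it and the finding does not depend on it.

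**Inflation to 700.** 605/0.95 = 637 and 605/0.90 = 673, so 700 covers the stated loss. The error is confined to the NPV figure.

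**The case against.** The strongest reply is that the result depends on the interval, and the article names none. Equal-tailed Jeffreys misses 99% only narrowly at 605 (98.98%), passes from about 618 participants, and reaches 99.12% at 700. A likelihood-ratio interval passes at 605. This stands as a caution: it is too strong to say that no interval could deliver the figure. It does not rescue the sentence, which is tied to 605 and describes an unqualified 95% CI.

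A second reply is that the article sets no success criterion on NPV. It describes expected precision for a perfect algorithm, from two inputs marked as approximate, and the eventual interval will come from the data. That is right: a lower limit below 99% would breach no pre-set rule, and the figure should not be called a target. It remains one of the two precision statements offered to justify the sample size.

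Third, the absolute gap is small, about 0.5 percentage points at 605 and 0.3 at 700. All participants are taken to hospital, so no one's care in the study rests on it. This is also true, and it is why the remedy is a correction of text, with no need to redesign the study. The gap matters for how the results can be used, since the quantity bounded is itself of the order of 1%.

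**Conclusion.** The statement is wrong as written. On the article's own inputs, with no false negatives, the two-sided 95% lower limit for NPV at 605 is about 98.5%, not above 99%. It is 98.6% at 630 evaluable and 98.7% if all 700 are evaluable. The corresponding upper limit on missed infarction among ruled-out patients is about 1.5% at 605 (1 − 0.9851 = 1.49%), half as much again as the 1% implied.

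The conclusion assumes a conventional two-sided exact or Wilson interval. It also holds at 605, with the stated 45% specificity, for one-sided exact, mid-P and equal-tailed Jeffreys limits. The sensitivity statement and the allowance for losses are sound.

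**What to change.** Restate the sentence in the Sample size section. With 605 evaluable participants, 10% prevalence, 45% specificity and no false negatives, the lower 95% limits are about 94% for sensitivity and about 98.5% for NPV (98.7% if all 700 are evaluable). Remove the claim of more than 99%, name the interval method, and use the same method when reporting results. Because the Introduction attaches 45% to the overall discharge fraction, confirm in the same sentence that 45% here means specificity.

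The cost is one sentence and a slightly less favourable stated precision. Enrolment, outcome and analysis are unchanged. If the sponsor prefers to keep a lower limit above 99%, the stated inputs imply about 909 evaluable participants by the exact method, or 957 to 1,010 enrolled at 5%–10% loss.
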